## Abstract

**Background:**

Supraspinatus tendon reconstruction (STR) was recently introduced as a new treatment option for irreparable posterosuperior massive rotator cuff tears (IPMRCT). STR was thought to be more advantageous than superior capsule reconstruction (SCR) for restoring supraspinatus (SSP) dynamics. However, there has been no prospective randomized controlled study on the early clinical efficacy of STR.

**Methods:**

A single-site, prospective, observers and patients double-blinding randomized controlled trial was designed. Fifty-eight patients aged 50–85 years with IPMRCT will be randomized 1:1 to receive either STR or SCR. The clinical outcomes were evaluated using the American Society for Shoulder and Elbow Surgery (ASES) score, range of motion (ROM), visual analogue scale (VAS) for pain, acromiohumeral distance (AHD), Goutlliar grade for fatty infiltration in the SSP, Sugaya grade for the autogenous fascia latas, isokinetic muscle strength testing and surface electromyography (EMG) testing for shoulder abduction muscle strength and complications.

**Discussion:**

The results of this study will contribute to the treatment algorithm of IPMRCT and assist surgeons in making treatment decisions. This is the first randomized controlled trial to compare the effects of STR and SCR for the treatment of IPMRCT.

**Trial registration:**

We registered the trial in chictr.org.cn on July 17, 2023 (register number: ChiCTR2300073716). Items from the WHO trial registry were found within the protocol.

## Administrative information

Note: The numbers in curly brackets in this protocol correspond with SPIRIT checklist item numbers. The items were grouped based on similarity (see http://www.equator-network.org/reporting-guidelines/spirit-2013-statement-defining-standard-protocol-items-for-clinical-trials/).

## Introduction

### Background and rationale {6a}

IPMRCT results in severe shoulder dysfunction and shoulder instability. SCR and bridging patches have been increasingly used to treat IPMRCT [1, 2]. In the SCR technique, the patch graft is fixed on the glenoid in the medial direction and on the footprint of the rotator cuff in the lateral direction. SCR technique was introduced as an innovative treatment for MRCT in 2013 [1] and achieved a long-term successful outcome [2]. SCR restored superior glenohumeral joint stability and then improved shoulder joint function [1, 3]. Retear rates were seen with partial cuff repairs (45%), graft interposition (21%) and SCR (21%), respectively [3]. As a whole, SCR was a validated, safe option compared with partial repair or simply physiotherapy. SCR was an inexpensive option too compared with reverse shoulder arthroplasty. However, SCR did not restore the anatomy or dynamic function of the SSP tendon. Bridging techniques with different patches that mimic the anatomy of the SSP tendon have been reported [2, 4]. However, this technique should be used carefully because of the high retear rate associated with the patch graft-tendon interface, the poor mechanical properties of allogenic grafts and the possibility of inflammation [4]. The STR technique using the autogenous fascia latas (FL) was recently introduced to treat IPMRCT [5]. The technique achieved a stable anatomic and dynamic reconstruction of the SSP tendon with fascia-muscle fusion. It was hypothesized that STR would have better clinical outcomes than SCR. However, there are still no reports of the clinical outcomes.

The intention of this study was to evaluate the clinical efficacy of STR for the treatment of IPMRCT in a prospective randomized controlled study to provide evidence-based medical evidence for its extensive development.

### Objectives {7}

The objectives of this trial were to compare the clinical effects of STR and SCR using autogenous fascia latas for the repair of IPMRCT. We hypothesized that STR would have a better clinical outcome than SCR.

### Trial design {8}

The trial is designed as a 1:1 randomized, controlled, observers and patients double-blinded single-centre trial with two parallel groups, which will compare the STR versus SCR using autogenous fascia latas for the repair of IPMRCT. The enrolled patients were randomized in a 1:1 ratio into two treatment groups (STR group and SCR group) by a simple computer-generated randomization system (https://castoredc.com). Double-blinding was used, in which patients and evaluators were blinded to minimize ascertainment bias. It was registered in the Chinese Clinical Trial Registry (ChiCTR.org ID: ChiCTR2300073716). The study protocol was approved by our institutional review board, and all subjects will be asked to finish a written informed consent. The flow chart of the inclusion and exclusion of trial participants is given in Fig. 1.

**Fig. 1 Fig1:**
[figure not shown]
CONSORT flow diagram of the progress of the study

## Methods: participants, interventions and outcomes

### Study setting {9}

The study will be conducted in the First Affiliate Hospital of Army Medical University China from Sep 2023 to August 2028. Patients with IPMRCT requiring arthroscopic surgeries will be transferred from our outpatient centre. After confirming the patient’s eligibility for inclusion and completing a baseline-level assessment, the investigator will give a detailed presentation of the study protocol and potential risks and answer all the questions raised by the patients. Each patient will sign an informed consent form. Upon enrolment, participants will be coded with a unique number.

### Eligibility criteria {10}

#### Inclusion criteria

Age 50–85 years old.Massive rotator cuff tear identified by preoperative MRI imaging technology (sagittal anterior and posterior tear length ≥ 5 cm or involving two or more rotator cuff tendon tears).The intraoperative evidence was IPMRCT (standard for irreparable rotator cuff injury: after full release, tissue forceps were used to test the tension of the broken rotator cuff stump, and it was found that the rotator cuff stump could not effectively cover the footprint under moderate pulling tension).Preoperative imaging examination Hamada classification within type 3.Agree to undergo arthroscopic STR or SCR operation.

#### Exclusion criteria

There is a previous fracture or nerve injury around the shoulder joint.Suffered cerebral infarction or cerebral haemorrhage in the past 6 months.Experienced unstable angina pectoris or myocardial infarction in the past 6 months.Psychiatric problems that precluded informed consent or inability to read or write.Preoperative infection.Complicated with other serious medical diseases.

### Who will take informed consent? {26a}

Patients with IPMRCT who met the inclusion will choose whether to join the clinical trial in the outpatient department. [name] will inform the patients with IPMRCT that they have met the inclusion criteria for the clinical trial. After confirming the patient’s eligibility for inclusion and completing a baseline-level assessment, the main investigator will give a detailed presentation of the study protocol and potential risks and answer all the questions raised by patients and their families. Each participant who meets all inclusion criteria and does not meet any exclusion criteria will sign an informed consent form. Upon enrolment, participants will be coded with a unique number.

### Additional consent provisions for collection and use of participant data and biological specimens {26b}

No biological specimens were collected, and we did not use participant data in ancillary studies.

### Interventions

#### Explanation for the choice of comparators {6b}

Mihata proposed SCR with the autogenous fascia latas in 2012 to treat irreparable MRCTs [6]. The SCR can restore the stability of the upper part of the shoulder joint and avoid excessive upwards movement of the humeral head and the impact of the shoulder peak. For irreparable MRCT, SCR can restore the stability of the upper part of the glenohumeral joint and the function of the shoulder joint.

STR involves the fixation of one end of the graft in the footprint and the other end in the medial spine of the scapula, with the aim of achieving muscle-fascial fusion by the 6^th^ postoperative week. Following STR, the SSP may transmit the contraction force to the humerus, thus restoring the anatomy and dynamic function of the rotator cuff. However, whether STR could achieve a better clinical outcome than SCR is still not known.

### Intervention description {11a}

The patient was placed under general anaesthesia in the contralateral decubitus position. Under cuff protection, the upper limb on the affected side was abducted by 30° and flexed at 20°. The vertical traction weight was 3 kg, and the lateral traction weight was 2 kg. The upper limbs on the affected side, neck and shoulders to the midline on the back side, nipple on the affected side of the ventral side, and autogenous fascia latas on the affected thigh were routinely disinfected.

The conventional posterior, anterior and anterolateral portal is selected and used. First, a 30° arthroscope (Smith and Nephew company) was placed into the glenohumeral joint from the posterior portal. The conditions of the subscapularis, labrum, articular cartilage and long head of the biceps are evaluated and repaired through the anterolateral portal. Then, the arthroscope was transferred into the subacromial space from the posterior approach to perform arthroscopic subacromial decompression, and debridement via the IPMRCT was confirmed arthroscopically.

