### Strategies to improve adherence to interventions {11c}

All surgical procedures were performed by the same senior doctor and the same 5-person group.

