### Concealment mechanism {16b}

The random assignment form is usually triplicated. Copies can be enclosed in an opaque envelope, with one copy provided to the patient, one copy to the researcher and one copy to the evaluator. The patient and researchers unseal it before surgery. The allocation scheme is not disclosed to the evaluators collecting outcome data throughout the study. The statistical analysts will also not know whether participants are in the STR or SCR group until the statistical analysis is completed.

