### Procedure for unblinding if needed {17b}

Because a surgical procedure is involved, the surgeons including the principal investigator were unblinded to the trial, and the evaluators collecting outcome data did not join the operation and were blinded throughout the study. When there is serious adverse event reporting and harms or the trial is finished, it will be unblinded.

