#### Quality control

To improve test reliability and reduce differences between operators, the following measures should be taken:Outpatient department by Chief Physician [name];Operations were led by [name].Photos and video recordings were taken for each operation.One person is responsible for the evaluation and statistical analysis of the test data.

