### Methods for additional analyses (e.g. subgroup analyses) {20b}

No additional analyses were performed.

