## Oversight and monitoring

### Composition of the coordinating centre and trial steering committee {5d}

The study will be performed by the Sports Medicine Center at Southwestern Hospital. There is no other coordinating centre. The trial steering committee consisted of the ethics committee of the First Affiliated Hospital of Army Medical University (No. AKY2022126) and the clinical research team. The research team consists of two principal investigators who oversee the study and are responsible for medical responsibilities, a study coordinator who plans patient visits, and an investigator who is responsible for data management and trial management. The research team meets weekly to assess progress, identify potential test subjects and work out logistical issues. A statistician was involved in the design of the trial and consulted on statistical issues throughout the study. Study leader [name] identified the enrolled patients in the outpatient department. A researcher collected general patient information. To improve the reliability of the test and reduce the differences between operators, the following measures were taken: All the operations were led by [name], and all the operations were photographed and recorded by video. The test data were evaluated and counted by one person.

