## Discussion

Irreparable MRCT presents a special challenge for both patients and surgeons alike. Both STR and SCR were introduced for the repair of irreparable MRCT. In this prospective randomized controlled trial, the application of STR and SCR in the treatment of large unrepairable rotator cuff defects was investigated to provide a more objective approach for the treatment of IPMRCT.

STR could restore the dynamic stability of the shoulder, and SCR could restore the passive biomechanical stability. The superior capsule plays a role as one of the static stabilizers, and superior stability is disrupted because of irreparable MRCT. SCR restored the stability of the glenohumeral joint superiorly at extremes of range of motion [6, 7]. STR and bridging techniques restore dynamic stability by restoring the anatomy and dynamics of the SSP [5]. The difference between STR and bridging techniques was the healing of the interface. In STR, fusion in the medial region is achieved between the graft and the SSP muscle; however, in bridging techniques, healing is achieved between the graft and the SSP tendon. Our unpublished data showed that fascia-muscle fusion is better than fascia tendon healing biomechanically and histologically.

Both STR and SCR achieved a good early clinical outcome. The effectiveness of SCR for repairing IPMRCT was verified [6, 8, 9]. Panzert, J reported that the surgical procedure of STR using open infraspinatus tendon shift and autologous biceps tendon interposition grafts resulted in the successful reconstruction of otherwise nonreconstructable MRCT in 2022 [10]; however, in fact, it was a tendon transfer, not a real STR. Ma and Zhou first reported an anatomical STR using an autogenous fascia latas for irreparable posterosuperior MRCT [5]. STR could transfer the strength of the SSP muscle to the rotator cuff insertion of the greater tubercle of the humerus. The clinical effect of STR is theoretically superior to that of SCR. Generally, STR used 5 anchors compared 6 anchors in SCR and might be less operation time. However, there are no cohort studies of STR or long-term clinical outcomes.

Limitations of this study is not a multi-center study. In addition, arthroscopic reconstruction of the supraspinatus muscle and upper articular capsule of the shoulder requires a learning curve. For surgeons who lack such expertise, surgical effectiveness may be affected.

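### The allocation is opened before surgery, so the unblinded surgeon decides the concomitant shoulder repairs knowing the arm; keeping it sealed until those decisions are written down closes a possible route to bias at little cost

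*Protocol article*

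**What the plan says.** Intervention description {11a} sets out a stage shared by both arms, before the separate STR and SCR descriptions. After the arthroscope enters the glenohumeral joint, "The conditions of the subscapularis, labrum, articular cartilage and long head of the biceps are evaluated and repaired through the anterolateral portal". Only then does the surgeon move to the subacromial space and confirm the irreparable tear. No threshold for repair is given for any of the four structures.

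On who knows the arm at that moment, Concealment mechanism {16b} says of the assignment form: "The patient and researchers unseal it before surgery". Procedure for unblinding {17b} adds that "the surgeons including the principal investigator were unblinded to the trial".

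On data, the operative items named under Outcomes {12} are operation time, blood loss and drainage volume. Neither the outcome list, Table 1 nor the data collection section {18a} names the concomitant repairs. The between-group comparison in {20a} is an unadjusted t test or Mann-Whitney U test, and {20b} states: "No additional analyses were performed".

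On source material, Quality control says "Photos and video recordings were taken for each operation", and section {5d} repeats that "all the operations were photographed and recorded by video". The oversight section also counts clinical medical records among the study data.

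**The concern.** A repair chosen during the operation is a co-intervention that takes place after randomisation. If the person choosing it knows the arm, the choice can depend on the arm, even without intent. The trial's stated hypothesis is that STR is better, and the same unblinded surgeon makes the choice in every patient.

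Subscapularis and biceps surgery can affect pain, rotation and function, which is what ASES, Constant-Murley, VAS and range of motion measure. If such surgery were used systematically more often in one arm, the STR-SCR difference would combine the effect of the reconstruction with that of the added procedures. The planned analysis would not separate the two, and no planned table would show the reader how often each repair was done in each arm.

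**Working it through.** **Order of events.** Setting the sections side by side:

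1. {16b}: the envelope is opened before surgery.
2. {17a} and {17b}: the surgeon knows the arm.
3. {11a}: the four structures are assessed and repaired in the glenohumeral stage.
4. {11a}, STR and SCR sections: only now does the technique differ between arms.

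The arm is therefore known at step 3, although as described nothing before step 4 depends on it. The concealment rule opens the allocation earlier than the operation needs.

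**The plan's own figure.** Inputs from Sample size {14}: SD 5.8, two-sided alpha 0.05, power 0.90, ASES 87.6 in the investigators' own SCR data and 93.1 as the best published SCR result. The implied difference is 93.1 − 87.6 = 5.5; the article does not state it as the target.

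- Normal approximation: n = 2 × (1.960 + 1.282)² × 5.8² / 5.5² = 23.4, so 24 per group.
- With the t distribution: 24.4, so 25 per group. The stated 25 is reproduced.

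**Possible size of bias.** The article gives neither the frequency of these repairs nor their effect on ASES. Both are assumptions here.

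Bias = (systematic difference between arms in the share repaired) × (ASES effect of a repair)

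| Difference in use | Effect 3 points | Effect 5 points |
|---|---|---|
| 10 percentage points | 0.3 | 0.5 |
| 20 percentage points | 0.6 | 1.0 |
| 30 percentage points | 0.9 | 1.5 |

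The middle case, 0.20 × 5 = 1.0 point, is 1.0 / 5.5 = 18% of the implied difference. The table runs from 0.3 / 5.5 = 5% to 1.5 / 5.5 = 27%.

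I stop at a 5-point effect because larger ones fit poorly with the SD used. With half the patients repaired, a 5-point effect contributes a variance of 5² × 0.25 = 6.25, or 19% of 5.8² = 33.6. An 8-point effect would contribute 16, about 48%, from these repairs alone.

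**Consequence for the test, if such a bias existed.** SE = 5.8 × √(2/25) = 1.64. Under no true difference, the two-sided rejection rate is Φ(−1.96 + b/SE) + Φ(−1.96 − b/SE):

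- b = 0.5: about 6%
- b = 1.0: about 9%
- b = 1.5: about 15%

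The nominal rate is 5%. These rates hold only if the difference in use is systematic.

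**The case against.** The strongest reply is that the article shows no arm-dependent use. The repairs stand in the common part of the operation, and "All surgical procedures were performed by the same senior doctor and the same 5-person group". That stands: the bias is possible, not demonstrated. A single surgeon removes variation between surgeons but does not prevent a choice that depends on the arm, because that surgeon knows it.

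A reader might go further and infer that the repairs are recorded nowhere, so that the trial could never tell whether they differed. The article does not support this. Every operation is photographed and filmed, and medical records are a data source, so the repairs can be recovered and counted by arm. Silence in Table 1 also proves little. The table omits drainage volume, the MRI gradings and adverse events, which the outcomes text says are collected, and the case report form is not shown. The statement under Data Availability that the article is the full protocol weakens this defence a little, but a missing form field or table is still detail rather than an error.

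A reader might also count chance imbalance in the repairs as bias. It is not: under randomisation the test's 5% error rate already allows for it. Only a choice that depends on the arm adds bias.

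Finally, a reader might think the operation-time comparison is spoiled. The common stage adds time in both arms and distorts the comparison only if it is used differently. The remark that STR "might be less operation time" is a comment in the Discussion, made beside an anchor count, not a planned claim.

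**Conclusion.** The point holds in a limited form. As written, the concealment rule lets an unblinded surgeon decide four kinds of concomitant repair with the arm known and without a stated criterion, and the article names those repairs neither as data nor as an analysis variable. This is an avoidable opening for bias, not evidence of bias.

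Its size cannot be derived from the article. About 1 ASES point against an implied 5.5 is an illustration, resting wholly on an assumed systematic 20-point difference in use and an assumed 5-point effect. If use does not depend on the arm, the bias is zero. The unadjusted randomised comparison is a valid primary analysis and is not criticised here. The case for acting is that the arm is opened before the operation needs it and that delaying it is cheap.

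**What to change.** 1. **Patients not yet operated on.** Amend Concealment mechanism {16b} so that the allocation stays sealed until the glenohumeral stage is finished and each concomitant repair has been decided and written down. This sets no rule on which structures to repair; it fixes only when the arm becomes known.
2. **Patients already operated on.** Extract the concomitant procedures from the existing operation records and video, ideally by someone who does not know the outcomes, and report them by arm as a description.
3. **Analysis.** Keep the unadjusted randomised comparison as primary. Do not make an adjusted model the main result: where the arm was already known, the repairs were chosen after allocation, and adjusting for them is debatable.

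**Cost.** A short pause in theatre before the allocated reconstruction, a review of existing records and video, and an ethics amendment, since section {25} sends changes of design back for approval. Trial status gives a recruitment start of 1 January 2024 and a planned end of 1 January 2026. Item 1 therefore helps only patients still to be operated on; if recruitment has closed, items 2 and 3 are what remain.

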#### STR group

The width of the autogenous fascia latas patch was measured from the anterior to the posterior edge of the rotator cuff tendon lesion. The length of the autogenous fascia latas patch was based on the distance from the lateral edge of the rotator cuff footprint and the distance from the most medial spine of the scapula. The thickness of the autogenous fascia latas was depended on the autogenous fascia latas, however, making sure this graft was 3 to 4 mm in thickness at least. If it is less 3 mm, longer autogenous fascia latas will be harvested and folded. Two absorbable anchors with a diameter of 4.5 mm (GRYPHON for the medial row and VERSALOK for the lateral row; DePuy Mitek Synthes, Raynham, MA) were placed on the medial line of the footprint. The anchors were sutured through the lateral autogenous fascia latas patch, which was 2 cm away from the lateral end, and the traction wire was sutured at the medial end of the autogenous fascia latas patch. The guide pin passed through the subacromial from the lateral portal, ran along the supraspinatus muscle to the most medial part of the spine of the scapula, and penetrated the dorsal skin. The traction wire was pulled medially to pull out the autogenous fascia latas patch under the acromion, and then the wire of the anchor was knotted to fix the autogenous fascia latas graft in a double-row style. A transverse incision of approximately 3 cm in length was made at the most medial side of the scapular spine to expose the medial end of the patch and the spine of the scapula. An absorbable lupine anchor with a diameter of 5.5 mm (Lupine, Depuy Synthes) was implanted at the most medial side of the scapular spine, and the autogenous fascia latas graft was sutured and fixed under the appropriate tension. The incision was sutured layer by layer, and the operation was completed.

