#### SCR group

For autogenous fascia latas, the size of the rotator cuff tear and superior capsule were evaluated in both the anteroposterior and mediolateral directions at 45 shoulder abduction by using a measuring probe. The width of the autogenous fascia latas patch was measured from the anterior to the posterior edge of the rotator cuff tendon lesion. The length of the autogenous fascia latas patch was based on the distance from the lateral edge of the rotator cuff footprint and the medial side of the superior glenoid. Autogenous fascia latas was fold for double layers and the thickness was guaranteed to be 6–8 mm. Two threaded anchors were inserted 5–6 mm above the medial side of the superior glenoid according to the surgical condition. Two anchors were inserted behind the midline of the scapula at the 10 to 11 o’clock and 11 to 12 o’clock positions. For the outer anchors, a double-row repair technique was performed on the footprint.

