#### Secondary outcome

Postoperatively, the improvement in shoulder function was evaluated. Additionally, the range of motion was recorded for shoulder joint active forwards flexion, abduction, lateral rotation, and internal rotation behind the back, with the latter recorded using vertebral levels ranging from C1 to S5, classified into grades 1–29. During the preoperative stage, as well as at 3 months, 6 months, 12 months and 24 months postoperatively, the VAS was employed to assess the improvement in shoulder joint pain.The Hamada classification was used to assess the degree of arthritis and measure AHD on anterior–posterior X-ray images during the preoperative stage, as well as at 3 months, 6 months, 12 months and 24 months postoperatively. During the preoperative stage, as well as at 3 months, 6 months, 12 months and 24 months postoperatively, Warner classification and Goutallier grading were employed on MRI oblique sagittal images to evaluate supraspinatus muscle atrophy and fatty infiltration. The integrity of the rotator cuff was determined using the Sugaya classification on MRI coronal images.The operation time and intraoperative blood loss were recorded immediately after the operation, and the postoperative drainage volume was recorded after the operation.

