## Assignment of interventions: blinding

### Who will be blinded {17a}

In this study, double blinding was used, in which surgeons were aware of the surgical protocol. Evaluators and patients were blinded, to minimize ascertainment bias.

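### As described, only STR leaves a wound at the medial scapular spine, and nothing in the plan hides it from the evaluator who grades internal rotation at the back, so the claimed evaluator blinding is unprotected.

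*Protocol article*

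**What the plan says.** Trial design {8} claims blinding of two parties: "Double-blinding was used, in which patients and evaluators were blinded to minimize ascertainment bias". Who will be blinded {17a} repeats it: "Evaluators and patients were blinded, to minimize ascertainment bias".

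The access wounds are described as follows.

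- Common to both arms (Intervention description {11a}): "The conventional posterior, anterior and anterolateral portal is selected and used".
- STR group: a guide pin "ran along the supraspinatus muscle to the most medial part of the spine of the scapula, and penetrated the dorsal skin". Then comes the open step: "A transverse incision of approximately 3 cm in length was made at the most medial side of the scapular spine". This incision is closed in layers.
- SCR group: medial fixation is at the glenoid, "Two threaded anchors were inserted 5–6 mm above the medial side of the superior glenoid according to the surgical condition". No wound on the back and no matching skin incision is described.

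Among the secondary outcomes, active motion includes "internal rotation behind the back, with the latter recorded using vertebral levels ranging from C1 to S5". Table 1 schedules range of motion and the Constant-Murley score before surgery and at 3, 6, 12 and 24 months, and abduction strength before surgery and at 6, 12 and 24 months. ASES and Constant-Murley are both named as primary.

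Two things support evaluator blinding. Concealment mechanism {16b} says the allocation scheme is not disclosed to evaluators, and Procedure for unblinding {17b} says they take no part in the operation. For patients, Study setting {9} says that "the investigator will give a detailed presentation of the study protocol and potential risks", and Concealment mechanism {16b} has the patient open the assignment before surgery.

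**The concern.** The arms differ by a mark on the skin that lasts beyond the operation. It lies on the upper back, and one of the evaluator's measurements is taken at the back. An evaluator who sees the scar and knows the two techniques can tell the arm, however well the allocation list is guarded.

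At stake are outcomes that need the evaluator's judgement: the Constant-Murley score (co-primary), range of motion and abduction strength. The protocol hypothesises that STR is better, and its Discussion calls STR superior in theory, so any expectation would plausibly favour STR. A blinding claim with nothing behind it also lends the result credibility that it may not have.

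**Working it through.** **The chain, step by step**

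1. *Do the arms differ visibly?* The three portals are shared. The pin exit through the skin of the back and the incision of about 3 cm appear only under STR. They follow from STR's defining step, fixing the graft at the medial scapular spine, so the difference is systematic. That SCR has no such wound is inferred: its text places medial fixation at the glenoid and mentions no wound on the back, but does not expressly exclude one.
2. *Does the evaluator work in that region?* Internal rotation is graded by vertebral level behind the back. It is recorded at four postoperative visits: 3, 6, 12 and 24 months.
3. *Would the stated protections hide the scar?* Non-disclosure of the list: no. Absence from the operation: no. No garment, patch, common dressing or check of blinding is described. Data Availability says the article is the full protocol, so there is little ground for assuming that one is set out elsewhere.
4. *Patients.* A patient who knows which operation uses the back incision could infer the arm. As written this adds nothing, because Concealment mechanism {16b} already has the patient open the assignment before surgery. The same section allots a copy of the form to the evaluator while saying that the scheme is withheld from evaluators.

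**What an undetected shift would do (illustration on ASES)**

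Inputs from Sample size {14}: SD 5.8 (the team's earlier SCR series) or 8.1 (the published SCR series), 25 per arm, two-sided 5%. The shifts of 1, 2 and 3 points are assumed; the protocol gives no estimate of bias.

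The plan's own figure first. The implied difference is 93.1 − 87.6 = 5.5 (inferred, not stated as the target). With SD 5.8 and 90% power, the t test needs 24.4, so 25 per arm, with power 0.907. The stated 25 reproduces.

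Next, with no true effect and a shift *b*:

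- Standard error = SD × √(2/25): 5.8 × 0.2828 = 1.64, and 8.1 × 0.2828 = 2.29.
- Noncentrality = *b* / standard error, 48 degrees of freedom, critical value 2.011.
- False-positive rate = probability that the absolute value of the noncentral t exceeds 2.011.

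| Assumed shift | SD 5.8: noncentrality | SD 5.8: rate | SD 8.1: noncentrality | SD 8.1: rate |
|---|---|---|---|---|
| 1 point | 0.61 | 9.2% | 0.44 | 7.1% |
| 2 points | 1.22 | 22.3% | 0.87 | 13.7% |
| 3 points | 1.83 | 43.3% | 1.31 | 25.0% |

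The table uses ASES because the sample-size section gives an SD only for ASES. ASES is patient-reported, so a shift in it would come through the patient and not through an evaluator seeing a scar. The evaluator route acts on Constant-Murley, motion and strength, for which the protocol gives no SD. The table shows how sensitive a trial of this size is to a small bias. It does not estimate the bias.

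**The case against.** Four points can fairly be made against this.

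- *The documents do not say the back is bare.* A reader might infer that blinding cannot hold, or is untrue for nearly every patient at every visit. The text does not support that: a vertebral level can be palpated through clothing, and the state of dress is not described. This objection stands. What can be said is that blinding is asserted without a means to protect it, and that the described procedures make unmasking likely.
- *SCR's lack of a wound on the back rests on silence.* True. The inference is nonetheless strong, because nothing in the SCR steps requires access at the medial scapular spine.
- *The patient half is weak.* Nothing says patients are told which incision belongs to which operation, and both arms have a posterior portal, so a wound behind the shoulder alone does not identify STR. This stands, and is overtaken by the opening of the envelope before surgery.
- *The rates are hypothetical.* True. A reader might also infer that no positive result could be told apart from bias. That goes too far: the implied planning difference of 5.5 points exceeds every shift assumed here.

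The objection does not remove the core. A systematic, visible difference between arms, an assessment at the back, and no concealment measure stand together in one protocol.

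**Conclusion.** The point holds as a gap in evaluator masking. As described, STR patients carry a wound of about 3 cm at the medial scapular spine and SCR patients do not, and neither stated protection conceals it. Unmasking of the evaluator is therefore likely, though not certain. Detection bias is possible in the co-primary Constant-Murley score, in range of motion and in strength. Its size is unknown; the false-positive rates of 7% to 43% depend wholly on assumed ASES shifts of 1 to 3 points and on which of the two SDs applies.

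Patient blinding fails as written because of the envelope procedure, whether or not the wound would give the arm away. The conclusion rests on two assumptions: that SCR is done without a wound at the medial scapular spine, and that no covering routine exists beyond what this full protocol describes.

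**What to change.** In Who will be blinded {17a} and Plans for assessment and collection of outcomes {18a}:

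1. Require the same opaque garment or patch over the scapular region in both arms at every evaluator assessment, with vertebral level palpated through it.
2. Instruct patients not to discuss wounds or allocation with the evaluator.
3. Record the evaluator's guess of the arm, and report it by arm.
4. Reconcile Concealment mechanism {16b} with Trial design {8} and Who will be blinded {17a}: who opens the envelope, and whether the evaluator receives a copy.
5. Describe the trial as evaluator-blinded only, unless patient masking can be achieved with ethics committee agreement. A dressing cannot hide a sutured wound from the patient, and limiting what patients are told about incision sites is a consent question.

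Cost: a protocol amendment and garments or patches, with no change to either operation and no extra visit. Vertebral-level readings become slightly less precise, equally in both arms. Trial status gives recruitment from January 2024 to January 2026 and completion in January 2028, so assessments still to come can be protected even if earlier ones were not.
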